**Methods:**

This is a prospective longitudinal cohort study of adult (≥18 years) acute medical hospital admissions with nested health economic and situation analysis in four hospitals: 1) Queen Elizabeth Central Hospital, Blantyre, Malawi; 2) Chiradzulu District Hospital, Malawi; 3) Hai District Hospital, Boma Ng’ombe, Tanzania; 4) Muhimbili National Hospital, Dar-es-Salaam, Tanzania. Follow-up duration will be 90 days from hospital admission. We will use consecutive recruitment within 24 hours of emergency presentation and stratified recruitment across four sites. We will use point-of-care tests to refine estimates of disease pathology. We will conduct qualitative interviews with patients, caregivers, healthcare providers and policymakers; focus group discussions with patients and caregivers, and observations of hospital care pathways.

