### Objectives

The primary objectives of this mixed methods (clinical, health economics and qualitative) study are:

*Clinical:* Determine the prevalence of multimorbid disease in adults admitted to hospital with acute medical conditions in Malawi and Tanzania.

*Health Economic:* Measure economic costs incurred and changes in health-related quality of life between admission and 90 days post admission.

*Situation analysis:* Describe current care for multimorbidity, enabling and hindering factors to the delivery of patient centred care.

We aim to use the findings to inform the development and design of a randomised controlled trial.

The secondary objectives are:

*Clinical:*

1.Measure prevalence of important pre-selected individual conditions, including chronic non-communicable (hypertension, diabetes mellitus and chronic kidney disease) and communicable (HIV infection) conditions.2.Measure hospital readmission rate 30 and 90 days after admission.3.Measure survival 30 and 90 days after admission.4.Measure a composite of readmission free survival 30 and 90 days after admission.5.Measure markers of disease control 90 days after admission.6.Measure the rate of end-organ damage (such as cerebrovascular accident and myocardial infarction).

*Health Economic:*

1.Disaggregate economic costs from patient and health system perspectives and sub-analyse according to the presence of multimorbidity and other socio-economic factors.2.Model how patients with different multimorbidity incur costs as they pass through the health system.3.Analyse changes in Health-related Quality of Life according to presence of different diseases.4.Estimate the potential cost-effectiveness of a selected intervention to improve diagnosis and treatment for people with multimorbidity.

*Situation Analysis:*

1.Describe healthcare pathways for adults during and after acute medical admission using structured observational data during patient admission.2.Qualitatively describe (i) patients’ level of health literacy related to their own conditions and (ii) healthcare engagement for patients with multimorbidity using key-informant interviews.

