*Phase 1 B: Health economic data sources and measurement*.** All consenting study participants will be asked asset ownership, house construction and demographic questions extracted from the most recent relevant national Demographic and Health Survey (DHS). Patient cost data will be captured before, during, and for 90 days after hospital admission using an amended version of the STOP-TB tool, a widely-used questionnaire for measuring TB patient costs
^
31
^. We will capture direct medical costs (
*e.g.*, drugs, diagnostics, consultation and inpatient fees), non-medical costs (
*e.g.*, food and transport), indirect costs (lost time for patients and guardians). Where a patient is readmitted to hospital, we will also capture these costs. Costs will be captured in local currency and presented in 2024 United States dollars.

Health system costs will be collected using top-down and bottom-up (micro) costing methods. We will develop and validate (with relevant hospital staff) a visual model of individual patient pathways through the study hospitals. This will be supplemented with data on waiting times, and time spent with various health workers from the sample of patients that are included in observations conducted as part of the situation analysis. Costs for each stage of the patient pathway (triage, admission, diagnostics, treatment, discharge, readmission
*etc*.) will be based on unit costs for tests, staff time, hospital bed days and other inputs, obtained from hospital data, tests and consumables suppliers, and Ministry of Health (MoH). Any other costs deemed relevant during the data collection stage will also be included. Top-down costing data on hospital overheads (utilities, building costs, maintenance,
*etc*.) will be obtained for each hospital.

HRQoL data will be collected using the EQ-5D-5L questionnaire in English, Chichewa (Malawi) and kiSwahili (Tanzania). The questionnaire will be administered, at admission, discharge, 30 and 90 days post admission in person or (day 30) by phone (as for patient costs).

**

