### Sample size

**
*Phase 1 A: Prospective longitudinal cohort study*.** The primary outcome will be disease prevalence. At 5% prevalence, a precision of 1.5% and power of 90% at α=0.05 is expected (precision will reduce as actual estimate rises towards 50%). We will use 5% prevalence as the lower boundary for inclusion of the disease during intervention development. We expect that HIV, hypertension and diabetes will meet this threshold. The cohort will allow us confidence to decide on the inclusion of chronic kidney disease. Prevalence will be assessed in both countries at the district and central hospital level to determine if findings are shared across settings. Given these assumptions, sample size is 1544 patients, with a target of 1600 to account for drop out. We will recruit these patients across the four hospitals (with numbers varying between sites due to different patient loads).

**
*Phase 1 B: Health economic evaluation*.** A randomised sub-sample of one third of the cohort study participants will be selected for participation in patient costing and HRQoL analysis (approximately 133 participants per hospital).

**
*Phase 1 C: Situation analysis*.** Sampling strategies for patients and caregivers is designed to include those individuals representing: those admitted for the first time and those who are returnees; those on HDU, ICU and ordinary wards; different age categories; male and female. We will ensure inclusion of patients with multiple known pathologies representing “multimorbidity” according to the final definition. Sample sizes for interviews are preliminary; they will continue until a point of saturation is reached.
Table 2 shows estimates of the number of patient and carer interviews required. For healthcare workers, we will include different cadres working in different departments.

**Table 2. T2:** Number of in-depth interviews, focus group discussions and structured discussions.

PER HOSPITAL SITE	In-depth interviews	Focussed group discussions	Structured discussions
Patients with multimorbidity *	10	24	10
Caregivers to patients with multimorbidity *	10	24	10
Doctors	2	-	4
Nurses	4	-	8
Ward attendants	2	-	6
Reception / frontline administration staff	2	-	2
Total	30	48	40

* Patients and caregivers will not be the same group during IDIs and FGDs. IDI, In depth interviews; FGD, focus group discussion.

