*e.g.*, lost time for paid or unpaid work, including housework) will be estimated based on the number of days of reported inability to work multiplied by the pre-disease wage given by patients during their baseline interview. The patient pathway model will be parameterised with unit costs and used to estimate individual patient and health system costs for a set of the most frequently observed multimorbidity combinations and patient types. Capital costs extending beyond one year will be annualised over their expected lifespan. Results will be presented as means and 95% confidence intervals. Deterministic and probabilistic sensitivity analyses will be conducted to test the robustness of the results. Multiple logistic regression will be used to compare patient costs by multimorbid condition(s) and wealth quintile to identify any significant differences. Additionally, we will examine the relationship between patient costs and age and sex. Change in HRQoL, expressed as QALYs, between admission, day 30 and day 90 interviews will be estimated using the area under the curve method. QALYs will be calculated according to the most relevant available tariff based on both geographical proximity and economic context. In our study we will use Uganda’s tariff for Tanzania, and Zimbabwe’s tariff for Malawi. Updated tariffs will be used if these become available before the analysis. The QALY calculations will also consider mortality during follow-up by attributing the lowest value from each value set (which corresponds to death), from the date of death until the end of the follow-up period. Missing patient cost or HRQoL data will be imputed using multiple chained imputations modelling with a predictive mean matching algorithm and relevant baseline variables.

Health economic analysis will be performed in Stata v15.4 and Excel.

**
*Phase 1 C: Situation analysis*.** Transcription and translation will be performed in line with local standard procedures. For accuracy, during the first 10 transcriptions a researcher will read the transcribed interviews and focus groups while listening to the audio recordings, and then check translations. Further checks will depend on the quality of these initial evaluations.

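### Participants who die are scored at the lowest EQ-5D-5L tariff value, which is the value of the worst living state and equals the value of death only if that minimum is exactly 0

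*Protocol article*

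**What the plan says.** The rule is in the Protocol article, Analysis, Phase 1B. Quality of life is summarised as follows: "Change in HRQoL, expressed as QALYs, between admission, day 30 and day 90 interviews will be estimated using the area under the curve method". Mortality is handled by "attributing the lowest value from each value set (which corresponds to death), from the date of death until the end of the follow-up period".

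Two borrowed tariffs are named: "In our study we will use Uganda’s tariff for Tanzania, and Zimbabwe’s tariff for Malawi". They are not final: "Updated tariffs will be used if these become available before the analysis". The instrument is given under Data sources and measurement: "HRQoL data will be collected using the EQ-5D-5L questionnaire".

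The result that the rule feeds is the primary health economic objective: "Measure economic costs incurred and changes in health-related quality of life between admission and 90 days post admission". Analysis of quality-of-life change by disease is a secondary health economic objective. The horizon is fixed in the abstract's methods: "Follow-up duration will be 90 days from hospital admission". The analysis uses a random third of the cohort, "approximately 133 participants per hospital".

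The article gives no minimum for either tariff and no expected mortality. Nowhere does it value death at 0.

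**The concern.** An EQ-5D-5L value set assigns a number to each living health state that the questionnaire can describe. Its lowest number belongs to the worst of those states. Death is not a questionnaire state; it is the fixed zero of the QALY scale. The parenthesis in the rule treats these two quantities as one.

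The rule applies from the date of death to day 90, so every death carries the substituted value for all its remaining time. The cohort is made up of emergency medical admissions. The protocol measures survival at 30 and 90 days and plans interviews with carers of patients who died, so deaths will occur. The error grows with the number and earliness of deaths. It therefore enters the overall QALY estimate, and it enters unequally for disease groups whose mortality differs. It also makes the score for being dead depend on which tariff is in use when the analysis is run.

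**Working it through.** **Stated figure.** The article gives no number on this point to reproduce. As a context check only, the target of 1600 gives 1600/3 = 533 participants in the health economic subsample and 533/4 = 133 per hospital, as stated.

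**Inputs**
- Horizon: 90 days from admission (article).
- Value after death: the tariff minimum, *m* (article). Its size is not given, so -0.1 to -1.1 is assumed, with 0 and +0.1 added to show the other cases.
- Day of death *t* and 90-day mortality *d*: not given, so assumed below.

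**Formulas**
- QALYs credited after a death on day *t*: *m* × (90 − *t*)/365. With death valued at 0, this term is 0 for any tariff and any *t*.
- Shift in the cohort mean: *d* × *m* × (90 − mean *t*)/365.

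**Multipliers**
- Death on day 7: 83/365 = 0.227.
- Death on day 30: 60/365 = 0.164.
- Cohort with *d* = 25% and mean day of death 20: 0.25 × 70/365 = 0.0479.

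| Assumed minimum *m* | Death on day 7 | Death on day 30 | Shift in cohort mean |
|---|---|---|---|
| +0.1 | +0.023 | +0.016 | +0.005 |
| 0 | 0 | 0 | 0 |
| -0.1 | -0.023 | -0.016 | -0.005 |
| -0.5 | -0.114 | -0.082 | -0.024 |
| -1.1 | -0.250 | -0.181 | -0.053 |

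**Scale.** Ninety days in full health is 90/365 = 0.247 QALY. A survivor at an assumed constant utility of 0.7 accrues 0.7 × 90/365 = 0.173. Against that survivor, the cohort shift runs from 0.0048/0.173 = 3% to 0.0527/0.173 = about 30%.

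**Comparison by disease.** Suppose two groups have 20% and 30% mortality, with deaths on day 10 (assumed). The rule adds (0.30 − 0.20) × *m* × 80/365 = 0.0219 × *m* to the difference between them. That is -0.002 at *m* = -0.1 and -0.024 at *m* = -1.1, on top of any difference that arises when death is 0.

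**The case against.** **The authors may have meant 0.** The parenthesis suggests that they wanted the value for death and worded it badly in a condensed article. That is possible. But the instruction points to the lowest value of each value set, so an analyst would look up a number in each tariff; a common 0 needs no lookup. If 0 was intended, the sentence still needs the same correction.

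**Direction and size are not in the article.** This stands. A reader might infer that the dead certainly accrue negative QALYs and that every death's loss is overstated. Both need a minimum below 0, and the article states none. A minimum of 0 gives no error, and one above 0 reverses its sign.

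**A Malawi–Tanzania artefact.** A reader might also infer that the rule creates a spurious gap between the countries. That needs unequal minima, which the article does not show. At 20% mortality on day 10 in both countries, assumed minima of -0.1 and -0.5 would give 0.20 × 0.4 × 80/365 = 0.018 QALY. A gap near 0.05 appears only if the two ends of the assumed range are placed in opposite countries. No between-country QALY contrast is listed among the objectives, and two different tariffs would make such a contrast tariff-dependent among the living anyway.

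**Carry-over to the Phase 2 cost-effectiveness model.** This is plausible, but the article does not say that these QALYs are the model's inputs.

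**Limited reach.** The objective is descriptive and uses a one-third subsample. The study hypothesis and the sample size rest on prevalence, which is untouched. This is true, but the affected result is still a primary objective. The planned sensitivity analyses and the EQ-5D caveat under Limitations do not address the value given to death.

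**Conclusion.** The rule is wrong as written. It equates the tariff minimum with death, and following it gives an incorrect post-death value unless that minimum is exactly 0. This conclusion needs no outside figure. It affects the primary QALY result directly, and the comparisons by disease to the extent that mortality differs.

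The size is conditional. With minima assumed between -0.1 and -1.1, a day-7 death is scored -0.023 to -0.25 QALY after death instead of 0. With 25% mortality at a mean of day 20, also assumed, the cohort mean moves by -0.005 to -0.053 QALY. The low end is minor beside a survivor's 0.17; the high end is not. The article does not establish that the bias is negative or that it differs between the countries.

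**What to change.** In Analysis, Phase 1B, state that utility is 0 from the date of death to day 90 under both tariffs and under any updated tariff. State that the lowest tariff value applies only to living respondents who report the worst health state. Delete the parenthesis that equates that value with death.

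The cost is one sentence in the plan and one line of code. Under Study status, the article reports that the study is in follow-up, that statistical code is still being developed and that no analysis has been performed. The correction can therefore be made before any result is seen, and no new data are needed.

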### Data management

Consent will be documented on paper or electronic forms. A paper copy will be given to the participant or guardian, and any original paper will be stored in a locked cabinet at the local hospital site, accessible only to the study team. All study data will be collected electronically.

Baseline, follow-up questionnaire data, and physiological observations (including pulse, respiratory rate, blood pressure, and oxygen saturations), and any point-of-care measures will be captured direct to Open Data Kit
^
32
^ software on devices with password encryption.

Clinical information including presenting complaints, history of presenting complaints, past medical history and drug history will be collected. Data on differential diagnosis and final diagnosis will be collected including clinical actions (
*e.g.*, prescribed medication) and patient response. We will also collect information on prescribed medication at hospital discharge, including where possible out of pocket expenses, health literacy and drug dispensary access (including stock outs).

Laboratory test results will be directly electronically exported from laboratory information systems where possible.

The study will adhere to LSTM (sponsor) data management and security policies, and encryption guidelines. This allows the data from each site to be collated, and presented at summary level in near real-time for the purposes of monitoring recruitment across both countries. During the study, individual participant level data will be available by the study team only, for the purposes of data validation and completeness checking. Access to this will be controlled by the same data security policies, with journaling of data change requests to allow full data audit.

After successful import of external data, and formal closure of the study, data will be fully anonymised by removing identifiers (including embedded electronic data) and granulating data which might enable an individual to be triangulated (area of habitation will be retained at “ward” level, and age rounded to the nearest year).

Data management for the patient costs, and HRQoL will be as per the clinical cohort study. Health system cost data will be collected and stored in custom built Excel spreadsheets.

**
*Qualitative data*.** Audio files will be stored on a secure network drive and transfer a copy to the project transcription and translation team using encrypted connection. Transcriptions and audio files will only be accessible to the study team. Any paper copies will be stored in a locked filing cabinet. Participant names will not be included in transcripts or file names; instead, participants will be given ID numbers.

Quality assurance measures will include piloting of the approaches described by the topic guides, and informal feedback from all participants on how to improve the structure, style and content of the sessions.

**
*Data availability*.** ODK will be used to collect data on Android devices. The data from all sites will be synchronised to a server hosted by the Malawi Liverpool Wellcome programme (MLW), Blantyre Malawi. Data will be of high quality and in a format that can be shared with other interested researchers through access of data dictionaries. Handling of data requests will follow the relevant standard operating procedures at MLW. All data will be managed according to a data management plan, and transferred in accordance with a data management plan.

### Ethics

Ethics was obtained from LSTM (21-086; approved on 10.05.2022); College of Medicine Research and Ethics Committee (COMREC), Malawi (P.11/21/3462; approved on 15.10.2021); National Institute for Medical Research (NIMR), Tanzania (NIMR/HQ/R.8a/Vol.IX/4008; approved on 13.05.2022); Kilimanjaro Christian Medical Centre (KCMC) (2570; approved on 15.12.2022).

Our reflexivity statement (available here: doi.org/10.7910/DVN/CKSYSW) describes how we have promoted equity in our international research partnership and authorship within the MultiLink Consortium
^
33
^.

## Dissemination of findings / results presentation

The findings from this study will be disseminated amongst the scientific community. Results will be feedback and discussed with hospital staff and patient groups. Within the MultiLink consortium, we have dedicated leads for both community and policy engagement, through community advisory boards and policy stakeholder ‘thinktank’ meetings. We intend to publish our findings in peer reviewed scientific journals and present data at appropriate local, national and international conferences. We will produce a close-out report for the local research ethics committees and LSTM (sponsors) at the end of the study and a final report once data are published. In addition, we will produce a lay report of our findings which will be made available to all participants. We will directly summarise the results to all ethics bodies, including COMREC. Data generated from this study will be used to inform design of a complex intervention in collaboration with key stakeholders as a part of structured dissemination activities.

### Study status

This study has started and is currently in the follow-up phase. Statistical code is under development for data analysis, which has not yet been performed.

## Limitations

There are a number of limitations with this study, which we have attempted to mitigate. First, there are a limited number of sites in two countries. In order to generate broadly generalisable results, the chosen sites reflect a mix of tertiary / referral hospitals and district hospitals in each country. Second, we have decided to systematically screen for four conditions (HIV, hypertension, diabetes and CKD) using point-of-care diagnostics. This may miss multimorbidity from other chronic conditions, which require additional infrastructure to confirm diagnoses (such as clinical imaging or enhanced laboratories), but we will collect clinical data on all diagnosed chronic conditions. A recent systematic review indicates a high burden of disease from these four conditions among hospitals patients, which can importantly be diagnosed using available point-of-care tools
^
24
^. Third, CKD diagnoses require evidence of chronicity of disease at three months and therefore data in this condition is prone to survivorship bias. Fourth, EQ5D-5L data and resulting QALY estimates may not reflect the most accurate picture of HRQoL in our study context. However, through our eCRF, we will collect rich clinical data with additional scales (such as the Patient Health Questionnaire-9 [PHQ-9] screening tool for depression
^
34
^; and clinical frailty scale
^
35
^ to explore the possible limitations and interrelationships. Fifth, our planned situation analysis will provide a cross-sectional picture of the health system at the time of the study, which is not able to incorporate the dynamic and adaptive nature of health systems. However, the MultiLink consortium includes researchers from each country and site, with a rich understanding of the context.

